### Statistical analyses

Descriptive statistics of the sample and the questionnaires’ scores will be computed. Pearson’s correlation coefficient will be used to evaluate the correlation between continuous variables at considered time points. Student’s t-test will be used to test the difference in mean patients’ pain, anxiety, depression, catastrophizing tendency, and resilience according to the SCS removal request. A bivariate linear mixed effect model for longitudinal data will be fitted to estimate the overall correlation between a psychological trait of interest and an intervention outcome over the entire course of observation [35].

All analyses will be carried out with the SAS software (SAS Institute, Cary, NC).

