## Materials and methods

### Primary aim

The primary aim is to study the associations between psychological variables and intervention outcomes (pain reduction, satisfaction, removal of SCS). We hypothesize that people with higher scores in anxiety and depression symptoms would report lower satisfaction with the SCS procedure and higher levels of perceived pain after the implantation of the device. Moreover, patients with higher levels of resilience may show lower removal requests. Finally, a greater tendency in catastrophizing pain symptoms may result in higher removal rates and lower levels of satisfaction with SCS.

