### Sample size

Considering that, on average, around 20–25 patients annually are admitted to the Palliative Care and Pain Therapy Division of the IEO for surgical implantation of an SCS to alleviate their pain symptoms, we anticipate enrolling a total of 50 patients within a 2-year study period. Assuming that the correlation between a psychological trait of interest (e.g., anxiety, measured by the STAI-Y) and an intervention outcome (e.g., pain intensity, measured by the BPI) at a specific time point is at least 0.4, the expected sample size will guarantee, with 80% of power, to reject the null hypothesis of no correlation with a 5% type I error. Given the exploratory nature of this study, no adjustment for multiple comparisons will be performed.

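### The aim names pain reduction as an outcome, but the stated pain analyses correlate scores without conditioning on T0 pain, so a pre-implant distress–pain link can appear as a post-implant finding

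*Protocol article*

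**What the plan says.** The protocol article's Primary aim reads: "The primary aim is to study the associations between psychological variables and intervention outcomes (pain reduction, satisfaction, removal of SCS". The pain hypothesis in the same section is worded as a level: patients with more anxiety and depression are expected to report "higher levels of perceived pain after the implantation of the device".

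For continuous variables, the Statistical analyses section states two methods. One is: "Pearson’s correlation coefficient will be used to evaluate the correlation between continuous variables at considered time points". The other is a bivariate linear mixed model to "estimate the overall correlation between a psychological trait of interest and an intervention outcome over the entire course of observation". Removal request is compared by t-test and is outside this point.

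The Sample size section assumes that the correlation between a psychological trait and "an intervention outcome (e.g., pain intensity, measured by the BPI) at a specific time point is at least 0.4", and claims that the expected sample is enough "with 80% of power, to reject the null hypothesis of no correlation with a 5% type I error".

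Under Patients' assessment, BPI is collected at T0 together with the anxiety, depression, catastrophizing and resilience scales, and again at T2 to T5. PGIC is collected at T2 to T5. Follow-up anxiety is the state form (STAI-Y1) only. The Conclusion hopes to recognise the patients who will have more difficulty adapting to SCS, so that support can be targeted.

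**The concern.** A reduction is a comparison with a starting value. The stated analyses and the power basis use pain at a visit, or pain pooled over all visits, with no reference to the T0 value. Suppose anxious patients already report more pain before implantation, and every patient then benefits to the same extent. Anxious patients will still report more pain at T5, and the correlation can be significant although anxiety has nothing to do with the benefit. The whole-course correlation does not remove this, because T0 is among the visits that it summarises.

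A second difficulty concerns same-visit correlations after implantation. They cannot separate distress that worsens pain from persistent pain that raises distress, and the state anxiety form used at follow-up is open to the second path.

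At stake is the use that the Conclusion has in mind. Identifying at T0 who will do poorly needs evidence about the course after T0, beyond what T0 pain already tells the clinician.

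**Working it through.** **1. The plan's own figure.** Inputs from the Sample size section: r = 0.4, 80% power, 5% type I error (two-sided assumed), 50 patients.

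- Required n = ((1.960 + 0.842) / atanh 0.4)² + 3 = (2.802 / 0.4236)² + 3 = 46.7, so 47.
- Power at n = 50: Φ(0.4236 × √47 − 1.960) = Φ(0.944) = 82.8%.

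The claim that 50 patients suffice is correct. It concerns a correlation of levels at one visit.

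**2. Main scenario.** The documents give no correlations, so these are assumptions: T0 anxiety with T0 pain 0.4, T0 pain with T5 pain 0.5, and no effect of T0 anxiety on T5 pain once T0 pain is known.

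- Implied correlation of T0 anxiety with T5 pain: 0.4 × 0.5 = 0.20.
- Partial correlation given T0 pain: (0.20 − 0.4 × 0.5) / √((1 − 0.16)(1 − 0.25)) = 0.
- Rejection rate of the unadjusted test at n = 50: Φ(atanh 0.20 × √47 − 1.960) = Φ(1.390 − 1.960) = 28.4%. Two simulations of 20,000 studies give 28.5% and 29.7%, so about 29%.
- Rejection rate of the test adjusted for T0 pain, by simulation: 4.8% and 5.1%.

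**3. Range over the assumed values.** Follow-up pain depends on T0 pain only, with regression to the mean (n = 50, 20,000 simulated studies per cell). Entries are rejection rates of the unadjusted test.

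| T0 anxiety–pain correlation | Pain stability 0.5 | 0.7 | 0.9 |
|---|---|---|---|
| 0.2 | 10% | 17% | 24% |
| 0.3 | 18% | 32% | 48% |
| 0.4 | 30% | 52% | 74% |
| 0.5 | 43% | 72% | 92% |

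The adjusted test stays between 4.6% and 5.3% throughout. The raw change score is not neutral here: at a T0 correlation of 0.4 it rejects in 10–29%.

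**4. Reduction unrelated to both T0 anxiety and T0 pain.** At a T0 correlation of 0.4 the unadjusted test rejects in 53–76% (17–25% at 0.2, 73–93% at 0.5). The change score and the adjusted test both stay near 5%.

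**5. T0 pain measured with error.** Stable traits correlated 0.4, reliability 0.6 to 0.8, the same benefit for everyone. T0 anxiety against T5 pain rejects in 40–63% unadjusted and in 12–13% adjusted for T0 pain; the change score stays near 5%. Over trait correlations of 0.3 to 0.6 the adjusted rate runs from 9% to 26%, still well below the unadjusted 24% to 95%.

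**6. Power of the adjusted analysis.** At partial r = 0.4 with 50 complete patients: Φ(0.4236 × √46 − 1.960) = Φ(0.913) = 81.9%.

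**The case against.** Four objections carry weight.

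- **The aim speaks of associations, and the study calls itself exploratory.** This is true, and the pain hypothesis is about a post-implant level, which a time-point correlation tests directly. A reader might infer that the aim formally asks whether distress predicts SCS benefit, or that the plan cannot test its own hypotheses. The text supports neither. What remains is that pain reduction is a named outcome, and exploratory status does not make a correlation of levels answer a question about reduction.
- **PGIC measures change.** Nothing in the Statistical analyses section excludes it from the Pearson correlations, and those would be less exposed. But it is perceived change, listed as a separate endpoint from BPI, and the example used for sizing is BPI intensity.
- **Covariates and derived variables may be set out in a fuller document.** They may, as may the random effects and time terms of the bivariate model, so no error rate is claimed for that model. The point rests on what the article does state: its analyses and its power basis.
- **Baseline adjustment is not perfect.** Step 5 shows inflation when T0 pain is measured with error, while step 3 shows the raw change score failing under regression to the mean. The choice is partly one of estimand.

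A reader might also take the power of about 83% as the rate at which same-visit T5 correlations would mislead. It is not a false-positive rate: it is the power to detect a T5 correlation that really is 0.4. If anxiety and pain each had stability 0.5 and nothing but the T0 association carried forward, the T5 correlation would be 0.5 × 0.4 × 0.5 = 0.10, significant in about 10% of studies.

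**Conclusion.** The point holds as a should-fix. The aim names pain reduction, while the stated pain analyses and the sizing do not refer pain to its T0 value. Under the main assumptions, T0 anxiety correlates significantly with T5 pain in about 29% of studies when it has no effect given T0 pain, against about 5% after adjustment. These rates depend on assumed correlations. Over the values tried, the unadjusted rate runs from about 10% to over 90%, lowest where the T0 association and pain stability are weak. The adjusted rate is near 5% if T0 pain captures the pre-existing link and higher if it is measured with error.

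It does not follow that every significant correlation in this study would be spurious. The planned correlations remain valid as descriptions of association. They cannot by themselves support a statement that T0 distress bears on pain reduction after SCS.

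**What to change.** - Define pain reduction relative to T0 BPI intensity, and reconcile that definition with the hypothesis, which is worded as a post-implant level.
- Add as the main pain analysis a regression of post-implant BPI intensity on the T0 psychological score with T0 BPI intensity as covariate, either at T5 or as a mixed model over T3 to T5. Report the slope or partial correlation with its 95% CI.
- Keep the Pearson correlations and the bivariate model, described as association and not as prediction of SCS benefit. State that same-visit correlations carry no direction.

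The cost is wording and one degree of freedom. All variables are already collected, and the article says that analysis will follow completion of data collection, so the change can be fixed beforehand. With 50 complete patients, power is about 82% at a partial correlation of 0.4. That is a different quantity from the unadjusted 0.4 in the Sample size section, and the revised text should say so.

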### Secondary aims

Additionally, this study will explore the acceptability and satisfaction levels regarding the SCS treatment and how this surgical procedure may affect patients’ perception of CP. Our hypothesis suggests that patients who report minimal improvement in CP levels may be more likely to request the removal of the device. Lastly, we will examine the perceived benefits of psychological counseling throughout the care pathway.

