### Endpoints

The following endpoints are assessed with self-report measures: pain intensity and pain interference (BPI), changes in perceived chronic pain (PGIC), anxiety (STAI-Y), depression (BDI-II), pain catastrophizing (PCS), and pain resilience (PRS).

Other endpoints are removal request (categorical: yes/no), and perceived benefit of psychological counseling (qualitative: open answer).

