#### Patients Global Impression of Change (PGIC).

The Patients Global Impression of Change is a brief self-report tool commonly used in routine clinical practice to assess the perceived change in pain experience after starting the treatment. The first 7-point item evaluates patients’ impression of change ranging from “very much worse” to “very much improved”. The second item evaluates the perceived change on a numerical scale ranging from 0 (“much better”) to 10 (“much worse”).

This instrument’s validity was verified in other clinical populations [27,28]. Recently, Perrot et al [27] reported significant correlations between PGIC and other well-established measures of pain intensity, and pain interference in daily life. and disease management efficacy, with a sample of neuropathic pain patients.

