### Patients’ assessment

Patients are assessed based on the following time points:

1) **Pre-surgical Assessment (T0)**

A psychologist evaluates the patient’s psychosocial status investigating the history of pain, how it affected psychological status, and social support. Moreover, patients’ resources in managing CP sequelae are assessed. At the end of the clinical consultation, the practitioner gives patients an information booklet about the SCS surgical intervention, the description of the two-step procedure, and any side effects.

After the consultation, patients receive a link with a set of questionnaires investigating patients’ perceptions of pain, state and trait anxiety, depression, and resilience. Moreover, the following questionnaires are administered: Brief Pain Inventory (BPI), Pain Catastrophizing Scale (PCS), Beck Depression Inventory II (BDI-II), State-Trait Anxiety Inventory (STAI-Y), and Pain Resilience Scale (PRS).

2) **Temporary SCS implantation (T1)**

After 2–4 weeks from T0, at the pre-surgical admission for the temporary SCS surgical intervention, a psychologist evaluates patients’ coping strategies and beliefs on the temporary SCS surgical procedure. The practitioner also assesses patients’ comprehension of the SCS implantation iter, and their expectations and he/she returns questionnaires’ results. The psycho-emotional status related to the imminent intervention is also explored and, if a significant amount of anxiety or worries is detected, further psychological support is provided.

3) **Permanent SCS implantation (T2)**

After one month from T1, a psychologist meets the patient during the pre-admission to implant the permanent SCS device. The practitioner assesses the patient’s pain perception and management and administers the following questionnaires: Brief Pain Inventory (BPI), Pain Catastrophizing Scale (PCS), and Patients Global Impression of Change (PGIC). Moreover, the perceived benefit of the provided psychological counseling is inquired with the following item: “Do you think that the psychological sessions have helped support you along the care pathway? If yes, in which aspects of your experience was it helpful?”.

4) **Follow-up time points (T3, T4, and T5)**

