At 1, 3, and 6 months from T2, patients receive a link with the following questionnaires: Brief Pain Inventory (BPI), Pain Catastrophizing Scale (PCS), Beck Depression Inventory II (BDI-II), State-Trait Anxiety Inventory (STAI-Y1), and the Patients Global Impression of Change (PGIC). Additionally, the Pain Resilience Scale (PRS) is administered at T3 and T5. Moreover, the perceived benefit of the provided psychological counseling is inquired with the following item: “Do you think that the psychological sessions have helped support you along the care pathway? If yes, in which aspects of your experience was it helpful?”.

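### The listed removal comparison uses mean pain and omits PGIC, so it tests the hypothesis linking minimal improvement to removal requests only indirectly

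*Protocol article*

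**What the plan says.** Secondary aims in the protocol article states a hypothesis about improvement: "patients who report minimal improvement in CP levels may be more likely to request the removal of the device". Endpoints defines the removal outcome as binary, "removal request (categorical: yes/no", and lists "changes in perceived chronic pain (PGIC") as an endpoint separate from BPI pain intensity and interference. The PGIC section says that the instrument serves to "assess the perceived change in pain experience after starting the treatment". It has a 7-point item and a 0 to 10 numerical item.

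Under Patients' assessment, BPI is collected at T0. At T2 the set is "Brief Pain Inventory (BPI), Pain Catastrophizing Scale (PCS), and Patients Global Impression of Change (PGIC"). At T3 to T5 it again includes BPI and ends with "State-Trait Anxiety Inventory (STAI-Y1), and the Patients Global Impression of Change (PGIC"). Both a change in BPI from T0 and PGIC will therefore be available at four visits.

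Statistical analyses names one analysis by removal status: "Student’s t-test will be used to test the difference in mean patients’ pain, anxiety, depression, catastrophizing tendency, and resilience according to the SCS removal request". The sentence names no instrument and no visit for pain, and it mentions neither PGIC nor change.

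**The concern.** Improvement and level are different quantities. On the 0 to 40 BPI intensity scale, a patient who falls from 36 to 20 has improved by 16 points, while one who stays at 18 has not improved at all. Yet the second patient has the lower follow-up score. A comparison of mean pain ranks these two the wrong way round for the stated hypothesis.

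Two errors follow. A real link between poor improvement and removal can be missed, because it is diluted when viewed through level. Conversely, a difference in level can be read as support for the hypothesis when requesters simply had worse pain from the start and improved as much as the others. Removal is an outcome in both the primary and the secondary aims, so the reading of this comparison matters.

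**Working it through.** **Does another listed analysis fill the gap?** Statistical analyses has three inferential components.

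- Pearson correlation is limited to continuous variables, and the removal request is yes/no.
- The bivariate mixed model pairs a psychological trait with an intervention outcome. It does not relate improvement to removal.
- The t-tests by removal request cover pain, anxiety, depression, catastrophizing and resilience.

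None names improvement against removal.

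**The plan's own figure.** Sample size states 50 patients and 80% power for a correlation of at least 0.4 at 5% type I error. By Fisher's z, two-sided, n = ((1.960 + 0.842)/atanh(0.4))² + 3 = 46.7, so 47, and power at 50 is Φ(atanh(0.4)·√47 − 1.960) = 82.8%. The statement is confirmed. It concerns one correlation at one visit and gives no assurance for the removal comparison, for which the article states no power.

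**Illustration of the dilution.** From the document: N = 50 and 5% type I error, taken here as two-sided. Assumed, because the article gives no values:

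- removal depends on improvement only;
- requesters differ from non-requesters by d = 1.0 SD of change;
- the T0-to-follow-up correlation ρ is 0.3, 0.5 or 0.7;
- the ratio k of the T0 SD to the follow-up SD is 1, 0.7 or 0.5;
- the number of requesters is 5 or 10.

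The absolute correlation of follow-up level with change is c = (1 − ρk)/√(1 + k² − 2ρk). For k = 1 this reduces to √((1 − ρ)/2). A difference of d in change then appears as c·d in level.

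| k | c at ρ = 0.3 | c at ρ = 0.5 | c at ρ = 0.7 |
|---|---|---|---|
| 1 | 0.59 | 0.50 | 0.39 |
| 0.7 | 0.76 | 0.73 | 0.71 |
| 0.5 | 0.87 | 0.87 | 0.88 |

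Power comes from the noncentral t distribution with 48 degrees of freedom and noncentrality c·d·√(n₁n₂/50). The root is √8 = 2.83 for 10 against 40 and √4.5 = 2.12 for 5 against 45. For change itself, c = 1.

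| Requesters v. others | Change | Level, k = 1 | Level, k = 0.7 | Level, k = 0.5 |
|---|---|---|---|---|
| 10 v. 40 | 79% | 19–38% | 51–56% | 67–68% |
| 5 v. 45 | 55% | 13–23% | 32–36% | 44–45% |

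A simulation of the k = 1 cases with 20,000 repetitions agrees to within about one percentage point.

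**The opposite error.** Suppose requesters are 1 SD worse at both T0 and follow-up, with the same improvement as the others. The level test then has d = 1.0 and rejects 79% of the time (10 v. 40) or 55% (5 v. 45), although improvement does not differ.

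**The case against.** The strongest reply is that Statistical analyses is one condensed paragraph of a journal article. It says pain, not pain level, and names no instrument or visit. Primary aim speaks of pain reduction, which is a change, so a change score could be meant, and a fuller protocol or analysis plan may say so. Nothing rules out comparing PGIC by removal status. This stands in part: the level reading is the most natural one but not the only one. It does not remove the point, because the article lists the variables for the removal comparison and that list does not match its own hypothesis.

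A reader might go further and infer that the hypothesis is not tested at all. The documents do not support that. The wording leaves room for a change score. Even on the level reading, follow-up pain is correlated with change (0.39 to 0.88 across the assumptions above), so the comparison is an indirect and weaker test. The PGIC section itself reports significant correlations between PGIC and pain intensity measures.

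The size is also open to challenge, and this objection stands. Entry requires VAS above 4, which may narrow the spread at T0, and a smaller T0 SD shrinks the loss considerably. The Discussion also names dissatisfaction, intolerance of the procedure and emotional distress as contributors to removal. If residual pain itself drives requests, level would be the stronger variable and change the diluted one.

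Finally, this is one secondary hypothesis in a study that calls itself exploratory, and no data are lost.

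**Conclusion.** The point holds in limited form. The listed removal comparison does not directly test the stated hypothesis. On its natural reading it uses pain level, a proxy confounded by baseline pain, and it leaves out PGIC, which the protocol presents as its measure of perceived change.

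The mismatch itself rests on the text. Its size does not: with 10 requesters, the loss from 79% ranges from about 11 percentage points (to 68%) to about 60 (to 19%), depending on the SD ratio and the correlation. All of these figures presume that improvement alone drives removal and that the group difference is 1 SD of change. The issue should be corrected before analysis. It does not threaten the study as a whole.

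**What to change.** In Statistical analyses, add a comparison of removal requesters with non-requesters on two measures:

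- PGIC, with a rank-based or ordinal method for the 7-point item, since a t-test suits an ordinal score poorly;
- BPI pain intensity change from T0, or follow-up BPI adjusted for T0 BPI.

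State the visit used, and require that it precede the request. Base any conclusion about improvement and removal on these comparisons. The comparison of mean pain level may stay as a separate exploratory result.

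The cost is a sentence or two of text and one or two more unadjusted tests in a study that already forgoes multiplicity adjustment. No new data are needed: BPI is collected at T0 and at T2 to T5, and PGIC at T2 to T5. The article reports data collection as ongoing, so the change can be made before the analysis.

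### The removal comparison does not require scores to precede the removal request, tests pain rather than pain improvement, and relies on a pooled t-test that is fragile if requesters are few and differ in SD

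*Protocol article*

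**What the plan says.** Removal of the device is one of three intervention outcomes in the primary aim. The Primary aim section expects that "patients with higher levels of resilience may show lower removal requests" and that stronger catastrophizing leads to more removals. The Secondary aims section expects that "patients who report minimal improvement in CP levels may be more likely to request the removal of the device". The Discussion reasons the same way, treating distress as something that contributes to the decision.

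The test is given in one sentence of Statistical analyses: "Student’s t-test will be used to test the difference in mean patients’ pain, anxiety, depression, catastrophizing tendency, and resilience", with patients grouped by whether they requested removal. It names no visit and sets no order between score and request. The Endpoints section defines the request only as yes or no.

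Under Patients' assessment, the instruments are scheduled as follows:

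- BPI and PCS: T0, T2, T3, T4 and T5.
- BDI-II and STAI: T0 and T3 to T5 (state form only at follow-up).
- PRS: T0, T3 and T5.
- PGIC: T2 to T5.

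T3 to T5 fall 1, 3 and 6 months after T2. The limitations list says that requests later than six months after the permanent implant are not captured.

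On size, the article says "we anticipate enrolling a total of 50 patients within a 2-year study period" and bases its power statement on a correlation that "at a specific time point is at least 0.4".

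**The concern.** A hypothesis that a trait leads to a request needs the trait measured first. The test sentence sorts patients by whether they ever requested removal and compares mean scores, while scores continue to be collected through the period in which requests arise. A score taken after a request may reflect the dissatisfaction behind it, or life after it. A T3 to T5 difference could then be reported as a predictor of removal when it is partly a consequence. The Conclusion hopes to recognise in advance the patients who will struggle with the device, so this distinction is central.

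The secondary hypothesis concerns improvement. The t-test list contains pain, but neither change in pain nor PGIC, the study's own measure of change.

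The choice of Student's pooled-variance test is a smaller matter. It becomes fragile if the requesters are a small group whose scores vary more, or less, than those of the other patients.

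**Working it through.** **Inputs.** From the article: N = 50, 5% type I error, 80% power, r = 0.4. Not in the article, and therefore assumed: the number of requesters m (3 to 25 of 50), the ratio k of requesters' SD to the others' SD (0.67 to 2), and a shift s in scores after a request (0.5 to 1 SD). Tests are taken as two-sided.

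**The plan's own figure.** By Fisher's z, n = ((1.960 + 0.842)/atanh(0.4))² + 3 = (2.802/0.4236)² + 3 = 46.7, so 47. At n = 50 power is 82.7%, and the correlation detectable with 80% power is 0.387. The statement that "the expected sample size will guarantee, with 80% of power" "to reject the null hypothesis of no correlation with a 5% type I error" is therefore sound, but for a correlation only.

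**Time order.** For a request made before T3, the only earlier BDI-II, STAI and PRS values are those from T0. Any later value of these scales for that patient comes after the request. The sentence on Pearson's correlation mentions time points without ordering them against the request. The mixed model spans the whole observation period. Neither supplies the order.

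**Effect of admitting post-request scores.** Suppose the groups do not differ before the request, and requesters' scores shift by s SD afterwards (pre–post correlation 0.6, 40,000 simulated studies; the 1.0 SD rows come from a separate run). A test on post-request scores then rejects about as often as a t-test with a true difference of s. Averaging one pre and one post score gives a standardised difference of (s/2)/√0.8 = 0.56s.

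| Requesters | Shift | Pre-request score | Post-request score | Mean of both |
|---|---|---|---|---|
| 5 | 0.5 SD | 4.9% | 18% | 9% |
| 5 | 0.8 SD | 5.0% | 38% | 15% |
| 5 | 1.0 SD | 5.0% | 55% | 22% |
| 10 | 0.5 SD | 5.0% | 28% | 12% |
| 10 | 0.8 SD | 5.0% | 60% | 24% |
| 10 | 1.0 SD | 4.9% | 79% | 34% |

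**Level of the pooled test.** The true variance of the difference is k²/m + 1/(50 − m). The pooled test estimates it as [((m − 1)k² + (49 − m))/48] × [1/m + 1/(50 − m)]. With m = 5 and k = 2, the true value is 0.80 + 0.022 = 0.822 and the estimate averages 1.25 × 0.222 = 0.278, so the variance is understated about threefold. With k = 1 both equal 0.222. Simulated type I error (normal scores, 30,000 runs per cell), pooled / Welch:

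| Requesters | k = 0.67 | k = 1 | k = 1.5 | k = 2 |
|---|---|---|---|---|
| 3 | 0.6 / 7.4% | 4.8 / 7.4% | 16.7 / 6.9% | 28.6 / 6.6% |
| 5 | 0.9 / 5.6% | 4.9 / 5.7% | 15.1 / 5.3% | 24.8 / 5.3% |
| 10 | 1.3 / 5.1% | 5.1 / 5.1% | 12.1 / 5.0% | 18.8 / 5.3% |
| 25 | 5.1 / 5.0% | 4.9 / 4.9% | 5.1 / 5.0% | 5.1 / 4.9% |

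With strongly skewed scores (gamma, shape 1.5; k = 1 or 1.5), Welch's test rejects about 12–13% of the time with 3 requesters and about 10% with 5.

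**Power.** The noncentrality is d√(m(50 − m)/50) on 48 degrees of freedom, and 80% power needs about 2.86. For m = 5, √4.5 = 2.12 and d = 2.86/2.12 = 1.35.

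| Requesters | Detectable difference (80% power) | Power at 0.8 SD |
|---|---|---|
| 3 | 1.70 SD | 26% |
| 5 | 1.35 SD | 38% |
| 10 | 1.01 SD | 60% |
| 25 | 0.81 SD | 79% |

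**The case against.** The best defence is that this is a short analysis paragraph in a journal article. Which visit feeds a t-test is often settled in the full protocol or the SAP, neither of which is shown. The test could be run on T0 scores alone without contradicting the sentence, and nothing states that post-request scores will be used. That stands as a limit: the article leaves the door open to reverse ordering but does not commit to it. It does not remove the point, because the article itself states both the directional hypotheses and the test, and the two do not match. The exploratory label is offered as the reason for not adjusting for multiplicity; it does not restore time order.

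A reader might also infer three stronger things that the documents do not support:

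- **That few requesters alone make Student's test unreliable.** They do not. With equal SDs it holds about 5% even at 3 versus 47. It fails only when unequal group sizes meet unequal SDs, and then in either direction.
- **That requesters will be few.** This is plausible with 50 patients, but the article gives no removal rate.
- **That a T3 to T5 difference would be wholly caused by removal.** The endpoint is a request. The article does not say whether or when the device then comes out, or whether requesters keep completing questionnaires. The 55% in the table needs a 1 SD shift, 5 requesters and a test on post-request scores, all assumed.

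It is also fair to say that pain in the test sentence is not expressly a level, and that PGIC data exist. Still, neither is tied to the removal comparison.

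**Conclusion.** The mismatch is real. The hypotheses are predictive, while the stated comparison has no time order and does not name improvement. How far this would mislead depends on how many scores follow a request and how much they shift. Under assumed shifts of 0.5 to 0.8 SD, false-positive rates on post-request scores are 18–38% with 5 requesters and 28–60% with 10, against about 5% on pre-request scores.

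The choice of test is a secondary, conditional weakness: 15–29% error with 3 to 5 requesters whose SD is 1.5 to 2 times larger, below 1% if their SD is 0.67 times as large, and no distortion if SDs are equal. Low power is the more certain cost. Even an even split of 25 and 25 detects only 0.81 SD, so a finding of no difference would carry little weight. The stated 80% power is not wrong; it belongs to a different test.

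**What to change.** In Statistical analyses:

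1. Compare T0 anxiety, depression, PCS and PRS between patients who later request removal and those who do not.
2. For the secondary hypothesis, use BPI change over an interval that is the same for both groups and ends before the request, such as T0 to T2, or use PGIC at T2. An interval ending at the last assessment before the request would not do, because non-requesters have no request date.
3. Exclude scores recorded after a request from these comparisons. This needs the date of each request; the article does not say whether it is recorded.
4. Replace the pooled Student's test by Welch's t-test or an exact rank test, noting that Welch's is only approximate with about 3 requesters or skewed scores.
5. Report differences with 95% confidence intervals, and state that the 80% power applies to the correlation and not to this comparison.

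Firth-penalised logistic regression, and a rule to call the analysis descriptive below about 10 requests, are optional.

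The cost is a few lines of analysis text and, if not already captured, one date per requester; data collection was still ongoing when the article was written. Power falls slightly if the SDs are in fact equal, change from T0 to T2 reflects only the temporary-device phase, and claims about removal become more modest.
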